### Data management and confidentiality

ParentApp is used offline with usage data stored on the device. When participants activate their data bundles, usage data and other in-app data will be automatically uploaded through end-to-end encryption to an IDEMS International server. Data will then be de-identified and shared with dedicated members of the research team by being uploaded to a secure server at the University of Oxford. Electronic records from remote data collection and in-person onboarding procedures will be exported from the respective platforms to a secure server at the NIMR, Tanzania, or the University of Oxford. This includes electronic records of audio recordings, transcripts, screening and consent forms, and participant tracking lists. Non-electronic data will be stored in locked filing cabinets at our local partners’ offices in Tanzania. Confidentiality will be maintained by delinking all personal identification in the final datasets used for analysis. All anonymised data will be kept for five years, in accordance with the University of Oxford’s ethical standards and all non-anonymised data will be disposed of after study completion.

### Data analysis

Quantitative data will be cleaned and analysed in R. Analyses will be conducted on an intention-to-treat basis, i.e., participants who have dropped out after enrolment will be included in the analysis. However, if there is significant dropout, we will exploratively analyse causal effects using complier average effects of components [71]. Patterns of missingness will be inspected, applying multiple imputation with fully conditional specification where appropriate [72].

#### Primary and secondary outcomes (Objective 1 and 2)

Generalised linear mixed effects modelling will be used to examine the main effect of each component level (e.g., those receiving sequential workshops versus those receiving non-sequential modules) on primary and secondary engagement outcomes. This approach includes a random intercept for clusters which will account for nesting of participants in neighbourhoods. The appropriate error distribution and link function will be selected for each outcome variable (e.g., overall app launches will be parametrised using a Poisson distribution; proportion of workshops completed will be parameterised using a Binomial distribution; proportion of home practice activities will be parameterised using a Binomial distribution). Main effects will be modelled as fixed effects and evaluated at the 0.05 significance level along with 95% confidence intervals. To assist the interpretation of effects, effect coding (where component levels take on the value of -1 or 1) may be applied [51, 74]. The regression will also include baseline covariates centred on the sample mean including caregiver gender and age, adolescent age, financial stress, and parenting behaviour such as child maltreatment.

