During the Preparation Phase, we conducted surface adaptations from the in-person PLH for Teens programme implemented in Tanzania [53], including condensing content from 14 to 12 sessions and using culturally appropriate illustrations that were gender-neutral, amorphous cartoon figures. Subsequent stages included iterative user testing with caregivers and adolescents from nine LMICs [54]. Results from the user testing demonstrated high satisfaction and acceptability of content. However, participants’ views on the app’s animated cartoons varied, with some finding them too juvenile. Participants also highlighted the need for regular reminders to encourage engagement. Following feedback from the user testing, we conducted a pilot study of intervention feasibility when delivered as a self-guided programme in low-income communities in South Africa. Findings from the pilot with 107 caregivers and nine implementing staff support those from the user testing; that the content is acceptable, relevant, and useful, and that the app is easy to use. Nevertheless, participant engagement in the pilot was low, with as little as 25% of recruited participants still engaging after the first session. Technical challenges and internet access were cited as some of the main difficulties for participants. Other feedback included wanting flexible access to content, and an alternative interface with human images. Participant feedback also suggested the need for an element of regular human support. Several adaptations were made following these findings and are being piloted in Tanzania, including testing the feasibility of remote support via one-on-one phone consultations and moderated WhatsApp groups.

Findings from the Preparation Phase as well as the larger digital intervention literature guided the selection of intervention components to be tested in the multifactorial experiment (see conceptual model in Fig. 1). The following criteria were used for component selection: each component must address at least one theoretical mediator associated with engagement with digital parenting interventions; each component must be unique from other components in terms of delivery mode, approach, or content; each component must contain at least some initial evidence in the literature; and each component and component level must be relatively low-cost and feasible for implementation in low-resource settings.

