#### Statistical power and sample size considerations for primary objectives

Given our focus on participant engagement and the intricate nature of the study design, we opted for a simulation-based approach to ascertain the appropriate sample size and statistical power [75]. We generated data for a 16-cluster randomised experiment with eight unique experimental conditions, varying the number of participants within each cluster (mean of 40, standard deviation of 8). We built the analysis model outlined above for each of the primary outcomes (i.e., overall app launches, proportion of sessions completed, and proportion of home practice activities started), estimating engagement rates and model parameters based on existing digital parenting intervention research (e.g., [32]), digital mental health interventions implemented in real-world settings (e.g., [36]), the original PLH for Teens cluster RCT in South Africa [13], and plausible scenarios based on observations from the ParentApp feasibility pilot. For each outcome model, 10,000 datasets were generated.

We estimated the minimum effect sizes needed to achieve ≥ 80% power for each of the primary outcomes while taking into account clustering and assuming an alpha level of 0.05. Poisson and Binomial distribution models were fitted for count and factor outcomes, respectively. Effect sizes were calculated as incidence rate ratios (IRRs) for Poisson distribution models and odds ratios (ORs) for Binomial distributions, which were averaged across all 10,000 replications. For overall app launches, the mean IRRs were 1.14 for support (WhatsApp), 0.91 for app design (sequential workshops), and 1.21 for digital literacy (on). For the proportion of sessions completed, the mean ORs were 2.18 for support (WhatsApp), 0.48 for app design (sequential workshops), and 2.35 for digital literacy (on). For the proportion of home practice activities started, the mean ORs were 3.13 for support (WhatsApp), 0.67 for app design (sequential workshops), and 2.31 for digital literacy (on). Based on these results, we determined that a sample of 640 participants would be sufficient to detect a significant effect in each of the primary outcomes.

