##### Objective 5: To conduct exploratory analyses to examine whether caregiver baseline characteristics (e.g., gender, age, financial stress and food insecurity, caregiver stress and depression, and parenting behaviour) are potential moderators of component effectiveness

In exploratory analyses, we will test the potential moderation of each component by socio-demographic information such as caregiver gender and age, as well as baseline severity of caregiver stress, depression, financial stress, and parenting behaviours. If appropriate, stratified analysis or effect modification will be used, adding interaction terms for the treatment component and the potential moderator [76] and considering separating effect modification into contextual and person-level effects.

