
##### Mitigating potential harm from intervention

We have also considered the potential risk of harm from participating in the intervention, and will be monitoring this throughout the project [79]. Participation in the parenting programme may potentially cause psychological harm for caregivers, particularly when they confront difficult experiences from their own childhood or deal with intimate partner violence at home. However, past research on parenting interventions, including numerous randomised trials conducted in LMICs [11], have consistently shown no evidence of harm and abundant evidence of benefits for both parents and children, as well as high levels of parent satisfaction. To ensure a comprehensive understanding of the potential outcomes of the parenting programme, this study will explicitly examine both the benefits and risks of the intervention. Our statistical analysis plan includes two-tailed tests to assess the differences between groups and examine potential positive and negative effects of the intervention. We will also use qualitative analysis to explore the experiences and perspectives of participants regarding the intervention and its effects.

We anticipate no direct harm as a result of withdrawing from the intervention, as participation in the programme is completely voluntary, with no direct penalties for non-participation. Furthermore, other studies, including evaluations in other low-resource settings [11], have shown no evidence of harm resulting from the termination of parenting interventions. In the unlikely event of significant harm being observed in any of the intervention conditions, we will suspend the implementation of the programme until the harm has been adequately addressed, and the programme has been modified accordingly.

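### The named Poisson and Binomial mixed models leave no room for variation between caregivers, so caregiver-level terms, including the Objective 5 moderator tests, would have standard errors that are too small

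*Protocol article*

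**What the plan says.** In the protocol article, the section on primary and secondary outcomes (Objectives 1 and 2) plans generalised linear mixed models. The choice of family is left partly open: "The appropriate error distribution and link function will be selected for each outcome variable". The examples that follow are specific: "overall app launches will be parametrised using a Poisson distribution; proportion of workshops completed will be parameterised using a Binomial distribution", and home practice is Binomial as well. The only random effect named is at neighbourhood level: "This approach includes a random intercept for clusters which will account for nesting of participants in neighbourhoods". Caregiver characteristics enter the same regression as covariates. Testing is stated as: "Main effects will be modelled as fixed effects and evaluated at the 0.05 significance level along with 95% confidence intervals", and the section on harm from the intervention adds that tests are two-tailed.

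The power section built this same analysis model for each primary outcome and fitted Poisson and Binomial models. It says: "We estimated the minimum effect sizes needed to achieve ≥ 80% power for each of the primary outcomes". For launches the resulting rate ratios are 1.14, 0.91 and 1.21.

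Objective 5 tests caregiver characteristics as moderators by "adding interaction terms for the treatment component and the potential moderator". It restates neither a family nor a random-effects structure. On the expected pattern of use, the Intervention section reports "as little as 25% of recruited participants still engaging after the first session" in the South African pilot.

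**The concern.** A Poisson model with a neighbourhood intercept says that two caregivers in the same neighbourhood with the same covariates differ in launches only by Poisson noise. A Binomial model with 12 trials says that one caregiver's 12 completions are independent given neighbourhood and covariates. Neither is credible for app use. Some people open an app daily and others hardly at all, and someone who stops early misses everything that follows. The protocol itself expects wide spread, since it plans to interview caregivers with at most 4, with 5 to 8, and with at least 9 workshops completed.

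The neighbourhood intercept can take up this excess only for effects that vary between neighbourhoods. Gender, age, stress and baseline parenting vary within neighbourhoods, and so do their products with a component. For those terms the standard error comes straight from the Poisson or Binomial variance. If that variance is too small by a factor φ, the standard error is too small by √φ. At stake are false moderator findings and intervals that are too narrow. The power statement for launches is also at stake if its data shared the same restriction.

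**Working it through.** **Inputs from the protocol.** 16 neighbourhoods, mean size 40 (SD 8), 8 per level of each component; 12 workshops and 10 home practice activities per caregiver; about 20% men; two-sided 5%.

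**Assumptions, because the protocol gives no figure.** Mean launches of 10 to 30; negative binomial k of 1 to 4 (variance μ + μ²/k, so a between-person CV of 1.0 to 0.5); within-person correlation ρ of 0.1 to 0.7.

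**Step 1: the plan's own figure.** The power statement cannot be reproduced uniquely, as no baseline rate or variance is given. The standard error at which a rate ratio reaches 80% power is |ln IRR| / (1.960 + 0.842), that is 0.047, 0.034 and 0.068 for 1.14, 0.91 and 1.21. Simulated pure Poisson data with mean 10 and neighbourhood SD 0.05 give power of 97%, 81% and 100%. The stated effects are therefore compatible with data that have no caregiver variation, but that does not show how they were generated.

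**Step 2: main effects.** With overdispersion, a neighbourhood's log mean has variance of about σ² + φ/(nμ). The fitted intercept variance picks up the excess (φ − 1)/(nμ). With n = 40, μ = 10 and φ = 6 this is 5/400 = 0.0125, an SD of about 0.11, even if neighbourhoods do not truly differ. Simulated type I error of the main effects was 11% to 15% with or without caregiver overdispersion. That inflation comes from z tests on 16 neighbourhoods, which is a separate issue; a neighbourhood-level t test on 12 df gave 4% to 6%.

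**Step 3: caregiver-level terms.** Dispersion is φ = 1 + (m − 1)ρ for m items per caregiver and φ = 1 + μ/k for counts. The rejection rate under a true null is 2[1 − Φ(1.96/√φ)].

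| Outcome | Assumption | φ | SE too small by √φ | Rejection |
|---|---|---|---|---|
| Workshops (12) | ρ = 0.1 | 2.1 | 1.4 | 18% |
| | ρ = 0.3 | 4.3 | 2.1 | 34% |
| | ρ = 0.7 | 8.7 | 2.9 | 51% |
| | ρ = 1 (ceiling) | 12 | 3.5 | 57% |
| Home practice (10) | ρ = 0.3 | 3.7 | 1.9 | 31% |
| | ρ = 1 (ceiling) | 10 | 3.2 | 54% |
| Launches | mean 10, k = 4 | 3.5 | 1.9 | 30% |
| | mean 10, k = 2, or mean 20, k = 4 | 6 | 2.4 | 42% |
| | mean 20, k = 1 | 21 | 4.6 | 67% |
| | mean 30, k = 1 | 31 | 5.6 | 73% |

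Simulations in the trial's design agree: 18% to 19% for workshops at ρ = 0.1 and 49% to 52% at 0.7; for launches 38% to 44% at φ = 6, 63% to 70% at mean 20 with k = 1, and 70% to 75% at mean 30 with k = 1. With no caregiver variation the rate is about 5%. Scaling the standard errors by the Pearson dispersion brings the overdispersed cases back to about 4% to 7%. Both results point to the missing dispersion as the cause.

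**Step 4: a drop-off pattern like the pilot's (assumed).** Suppose 75% complete one workshop and 25% are spread evenly over 2 to 12. The mean is 0.75 × 1 + 0.25 × 7 = 2.5. The variance is 0.75 × 1 + 0.25 × 59 − 2.5² = 9.25. The Binomial variance is 2.5 × 9.5/12 = 1.98. So φ = 9.25/1.98 = 4.7, and a nominal 5% test rejects about 36% of true nulls.

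**Step 5: power for launches.** At mean 10 and neighbourhood SD 0.05, adding k = 2 lowers GLMM power at the stated rate ratios from 97%, 81% and 100% to 61%, 41% and 87%. With the 12-df neighbourhood-level test the fall is from 92%, 68% and 100% to 45%, 25% and 72%. For workshops (completion 30%, neighbourhood SD 0.5), ρ = 0.4 lowers GLMM power only from 89%, 87% and 95% to 86%, 81% and 90%.

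**The case against.** There are four fair points on the other side.

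- Poisson and Binomial are introduced as examples under a promise to choose an appropriate distribution, and a statistical analysis plan that is not shown may contain a dispersion check. This stands as a reason to call the choice correctable. It does not remove the point, because these are the only families named and the power section fitted them.
- The section that names the models is about component main effects, where this mechanism adds no material type I error. That stands in full.
- Objective 5 restates no model, and it is exploratory. Moderators are not a step in the component selection under Objective 8. That also stands. An exploratory label does not justify intervals that are too narrow by a factor of about 1.4 to 5.6, but it does limit the damage.
- The pilot gives one drop-off figure and no launch counts or completion distribution. It makes dependence within a caregiver very likely and says nothing exact about its size.

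A reader might infer more than this supports. One could read a single error rate, such as 64%, as a property of the plan. It depends on assumed dispersion, and for the 12-workshop outcome it is out of reach because φ cannot exceed 12. One could also read the Discussion as committing to act on moderators. It says only that findings may identify moderators that could add to understanding of subgroups such as fathers.

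**Conclusion.** The point holds for caregiver-level terms. If the named models are used unmodified, standard errors for baseline caregiver covariates and for the Objective 5 interactions would be too small. The main-effect tests and the component selection are not exposed to extra false positives by this route.

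The size is conditional on dispersion that the protocol does not give. For workshops, null rejection at a nominal 5% runs from about 18% to about 50% for within-person correlations of 0.1 to 0.7, with a ceiling near 57%. For launches it is about 40% at φ = 6 and about 75% at mean 30 with k = 1; the mildest case examined, mean 10 with k = 4, gives about 30%.

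For the primary objective the consequence is one of power, and only if the simulated data had no caregiver variation, which the article does not state. In that case the launch rate ratios of 1.14, 0.91 and 1.21 are optimistic as effects detectable with 80% power.

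**What to change.** - **Launches and ParentPoints:** name a negative binomial mixed model with the neighbourhood intercept.
- **Workshops (completed and started) and home practice:** name a beta-binomial model, or add a caregiver-level random effect to the Binomial model, again with the neighbourhood intercept.
- **Scope:** use these for the engagement outcomes in Objectives 1 to 3 and 5, and say so explicitly under Objective 5. Choose families separately for time on the app, which is not a count of events, and for the Objective 4 behavioural outcomes, which include summed frequency scores and a yes/no item.
- **Power:** state whether the simulated data contained caregiver-level variation. If they did not, regenerate them with it over a stated range of dispersion and restate the detectable effects.

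The cost is one dispersion parameter per model and a rerun of existing simulation code. The detectable effects, chiefly those for launches, may turn out less favourable.

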To account for contamination and potential confusion that could arise if participants learn about the different experimental conditions, random assignment to conditions will be clustered. We will randomly allocate 16 low-income neighbourhoods in Mwanza City, Tanzania, to eight different treatment combinations (*N* = 16 clusters, approximately 40 caregivers in each cluster, approximately 640 caregivers in total). Two clusters will be allocated to each experimental condition with approximately 80 families per condition. Although this factorial trial has eight different combinations of the three intervention components, it is important to note that each component will be evaluated by comparing all caregivers receiving one component to all caregivers not receiving that component. Compared to a traditional RCT, this design is highly efficient as it enables the testing of several components simultaneously, requiring a smaller sample to test their effects [42].

In addition, this study will also assess the barriers and facilitators to engagement qualitatively via interviews and focus groups discussions (FGDs) with a subset of low, medium, and high engaging participants (*N* = 30). This qualitative approach allows for the investigation of caregivers’ subjective engagement with the intervention, providing a nuanced understanding of their perceptions about the feasibility and acceptability of intervention components and the contextual factors influencing engagement. Using the component selection methods outline by Collins and colleagues [51] in conjunction with qualitative findings, we will identify an intervention package for ParentApp which is optimally effective, cost-effective, and feasible for low-income families in Tanzania. The optimised intervention package will subsequently be evaluated in a two-arm RCT.

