#### Exploratory analyses

##### Objective 3: To conduct exploratory analyses to examine whether there are any interaction effects between components on primary and secondary engagement outcomes

We anticipate that there will be some interactions (synergistic effects) between component levels. In exploratory analyses, we will examine a fully saturated generalised linear mixed effects model which includes all three main component effects, as well as two-way and three-way interactions. This model will be replicated for each of the primary and secondary outcomes. However, interaction effects will not be considered in the final component level selection process due to potential power constraints.

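### Three cluster-level components are tested at 0.05 in a mixed model on 16 clusters with no small-sample method named; under the usual large-sample tests the main-effect type I error would exceed 5%

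*Protocol article*

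**What the plan says.** On design, the Overview of the study states: "Two clusters will be allocated to each experimental condition with approximately 80 families per condition". Each component is constant within a neighbourhood, so each main effect compares eight clusters with eight.

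On analysis, the section on primary and secondary outcomes (Objectives 1 and 2) specifies a generalised linear mixed model: "This approach includes a random intercept for clusters which will account for nesting of participants in neighbourhoods". As an example of the error distributions, "overall app launches will be parametrised using a Poisson distribution"; the two proportions are Binomial. The inferential rule is: "Main effects will be modelled as fixed effects and evaluated at the 0.05 significance level along with 95% confidence intervals". The harm section adds that tests are two-sided: "Our statistical analysis plan includes two-tailed tests to assess the differences between groups". The software is R, with no function named.

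For Objective 3, "we will examine a fully saturated generalised linear mixed effects model which includes all three main component effects", together with all two-way and three-way interactions. That model is exploratory, and its interactions are excluded from component selection.

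On sample size, "We generated data for a 16-cluster randomised experiment with eight unique experimental conditions". The same analysis model was fitted, with alpha 0.05 and a target of at least 80% power. No check of type I error is reported.

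Under Objective 8, a significant main effect is the first step in choosing a component level. Without one, the lower level, or the level expected to do worse, is kept.

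**The concern.** Information on a cluster-level factor comes from 16 cluster summaries, and recruiting more caregivers per neighbourhood does not add to that number. An intercept and three main effects leave 12 residual degrees of freedom; the saturated model leaves 8. Standard mixed-model output relies on large-sample theory in the number of clusters. Maximum likelihood understates the between-cluster variance by dividing by 16 rather than by the residual df, and a normal or chi-squared reference ignores that the variance is estimated.

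The selection rule is at stake. A test with a true level of around 10% would pass ineffective component levels forward more often than the stated 0.05 suggests. The cost-effectiveness and qualitative steps that follow do not ask whether the effect is real. If the power simulation used the same uncorrected test, its power is overstated as well.

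**Working it through.** **Inputs from the protocol article.** 16 clusters, 8 conditions, 2 clusters per condition; cluster size mean 40, SD 8; two-sided alpha 0.05; random cluster intercept; Poisson or Binomial error.

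**Assumed, because the article does not give them.** Random-intercept SD 0 to 0.8; mean of 20 launches; 25% completion; with and without person-level overdispersion.

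**The plan's own figure.** 16 × 40 = 8 × 80 = 640, which reproduces. The power of at least 80% cannot be rebuilt, because the between-cluster variance and baseline rates are not stated.

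**Residual cluster df.** Main-effects model: 16 − 4 = 12. Saturated model: 16 − 8 = 8.

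**Analytic type I error**, treating the 16 cluster summaries as approximately normal:

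- ML variance with Wald z. The variance is RSS/16 instead of RSS/df, so the rate is P(|t_df| > 1.96 × √(df/16)). For 12 df the cut-off is 1.697, giving 11.5%. For 8 df it is 1.386, giving 20.3%.
- Likelihood ratio test. Rejection when 16 × ln(1 + t²/df) > 3.84, i.e. |t| > √(df × (e^(3.84/16) − 1)). For 12 df the cut-off is 1.805, giving 9.6%. For 8 df it is 1.473, giving 17.9%.
- Unbiased variance with z. P(|t_df| > 1.96) is 7.4% for 12 df and 8.6% for 8 df.

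**Simulation** (1,500 null trials per scenario; mixed model fitted by ML with adaptive quadrature; Wald z at 1.96; no individual-level covariates):

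| Setting | Main effects | Saturated model |
|---|---|---|
| Cluster variance or overdispersion present, Wald z | 9.8-12.8% | 17.6-21.0% (14.1% at Binomial cluster SD 0.1) |
| Neither present, Wald z | 4.6-5.3% | 4.4-5.2% |
| ML standard errors with t reference, variation present | about 7-9% | about 8-15% |
| Cluster-level regression on t with 12 or 8 df | 4.2-5.5% | 4.2-6.0% |

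Person-level overdispersion with zero cluster variance (Binomial scenario) already gave 11.2% for main effects. The chance of at least one false positive among the three components was about 26-33% per outcome wherever some variation was present.

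**Power.**

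- A valid t test on 12 df needs a noncentrality of about 2.18 + 0.87 = 3.05 for 80% power.
- A known-variance z test needs 1.96 + 0.84 = 2.80. The ratio 3.05/2.80 is 1.09.
- ML Wald z reaches 80% at 2.55. The ratio 3.05/2.55 is 1.20.
- On the valid t test, an effect at 2.55 has 65% power, and one at 2.80 has 73%.

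**The case against.** The strongest objection is that the article does not prescribe the faulty procedure. It names a model, a significance level and an interval level, but not maximum likelihood, Wald z or any reference distribution. A small-sample t test or a permutation test would also be read at 0.05. The article refers to a statistical analysis plan that is not shown, and such details often sit there.

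This stands in part. A reader might infer that the trial's false-positive rate simply is 10-13%. The documents do not support that: the figure is conditional on the test used and on some cluster variance or overdispersion. What survives is that every usual large-sample way of carrying out the stated model exceeds 5% once such variation exists. The article also does not leave the matter wholly open. It fixes the model and level, bases selection on the result, and reports a completed sample-size simulation from that model.

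A reader might also take the roughly 20% rate as the headline. It belongs to the exploratory saturated model, whose interactions the article excludes from selection.

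Finally, a significant effect selects a level only provisionally, and the chosen package goes on to a further trial. That limits the harm from one false positive but does not correct the error rate.

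**Conclusion.** The point holds conditionally. With 16 clusters and 12 residual cluster df, the usual large-sample tests give a main-effect type I error of about 10-13% (ML Wald z), about 10% (likelihood ratio) or about 7% (unbiased variance with z), and the 95% intervals under-cover to match. This requires some between-cluster variance or person-level overdispersion, which is realistic for app-usage counts; without either, the rate is about 5%. The exploratory saturated model would be worse, at about 18-20% with ML Wald z or a likelihood ratio test, but that does not bear on selection.

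A reader might infer that the true power is 65%. That follows only if the simulation used an uncorrected ML Wald z test and the effect sat exactly at 80% power under it; the article does not say which test was used. Covariate adjustment was not simulated, so the figures are for the unadjusted model.

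**What to change.** Specify one small-sample-valid test and matching 95% interval for each component main effect. Any of these would serve:

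- a covariate-adjusted cluster-level analysis on t with 12 df (8 df if saturated);
- a mixed model with both a variance correction and a df correction, since a t reference with ML standard errors still gives about 7-9%;
- a permutation test of each component that permutes clusters within levels of the other two. Each of the four strata holds four clusters, two per level, so there are 6⁴ = 1,296 arrangements, ample for a 0.05 test. Freely re-allocating all 16 clusters across the eight conditions is not an exact test of a single main effect when other components work.

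Then confirm that the sample-size simulation used the chosen test, or rerun it and restate the power or minimum detectable effects.

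No change to recruitment, clusters or data collection is needed; the cost is analysis text and possibly a rerun of the simulation. The detectable effect on the log scale rises by about 9% against a known-variance z test and about 20% against ML Wald z.
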